### Proposed data analysis

Groups will be compared at baseline regarding the important prognostic indications: donor site location, depth, size, age, skin type and time since graft. Data will be entered into IBM SPSS 22.0 for Windows software files (IBM, Armonk, NY, USA) and tested for normality of distribution. Descriptive statistics for all variables will be computed. If parametric statistics are able to be used, a two-way analysis of variance for group × time interaction will be performed to compare skin thickness between normal, donor and scar sites with a planned least significant difference post hoc analysis. Significance will be set at *p* < 0.05. If raw data are not normally distributed, an equivalent non-parametric analysis will be used [40].

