**Methods/design:**

This study is a single-centre, single (assessor)-blinded, randomised control trial in patients with burns donor sites to their thighs. Patients will be randomly allocated to a control group (with no compression to donor sites) or to an experimental group (with compression to donor sites) as the comparative treatment. Groups will be compared at baseline regarding the important prognostic indicators: donor site location, depth, size, age, and time since graft (5 days). The IPG treatment will be administered post-operatively (on day 5). Follow-up assessments and garment replacement will be undertaken fortnightly for a period of 2 months.

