### Randomisation

Randomisation will be achieved through computerised tabulation with concealed allocation to each participant via a sealed envelope method. Participants will be randomly allocated into one of two groups: a control group that will have no compression to donor sites (the standard existing treatment) or an experimental group that will be provided with compression to donor sites (the comparative treatment).

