### Intervention

The treatment will be IPG objectively measured in millimetres of mercury using the PicoPress® pressure sensor (mediGroup Australia, Melbourne, Australia) [29], and it will be administered post-operatively between days 3 and 5. Participants in the treatment group will be asked to wear the IPG for 23 h/day for a period of 8 weeks. Individual wear time for the IPG will be established through completion of a daily log book for the treatment group. Participants will commence involvement in the study as inpatients on the burn ward and may progress to the outpatient clinic during the study as per normal hospital procedure. Once discharged from the inpatient burn ward, participants will return to the hospital for fortnightly study measurements. Both groups will be reviewed every 2 weeks over the 2-month period to check scar and/or IPG quality (in millimetres of mercury). Surgical intervention, wound care dressings, medication, nutrition, exercise and nursing management of the donor site will be standardized between groups, the sole difference being that one group will have compression therapy for their donor site and the other will not.

The principal investigator will record demographic information, including age, skin type (as assessed using Fitzpatrick skin typing) [30], cause of injury, TBSA burned, depth of injury, surgical procedure undertaken, medication used and time taken to heal (including number of dressing changes and types of dressings used). Smoking status (which may impact on wound healing) will also be recorded. The donor will be considered healed when there is no raw, open or oozing epithelium. A second researcher blinded to the intervention will complete all outcome measures.

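### The named thickness analysis has no covariates, and the prognostic factors serve only a baseline comparison, so between-arm contrasts give up precision and protection from chance imbalance

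*Protocol article*

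**What the plan says.** The Proposed data analysis section of the protocol article opens with the prognostic factors: "Groups will be compared at baseline regarding the important prognostic indications: donor site location, depth, size, age, skin type and time since graft". The Abstract (Methods/design) repeats the idea: "Groups will be compared at baseline regarding the important prognostic indicators". Neither place gives these factors a further use or says what follows if the arms differ.

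The same section then names the model: "a two-way analysis of variance for group × time interaction will be performed to compare skin thickness between normal, donor and scar sites". The fallback is equally bare: "If raw data are not normally distributed, an equivalent non-parametric analysis will be used". Neither includes a covariate. Normal-skin thickness appears only as one of the sites to be compared.

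The Randomisation section reads: "Randomisation will be achieved through computerised tabulation with concealed allocation to each participant via a sealed envelope method". It mentions no stratification or minimisation. The Intervention section shows that candidate covariates are collected: "The principal investigator will record demographic information, including age, skin type", and also "Smoking status (which may impact on wound healing) will also be recorded". No role in the outcome analysis is stated for them.

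**The concern.** After concealed randomisation, a comparison of the arms at baseline describes chance. It neither corrects an imbalance nor sharpens the treatment estimate. A variable believed to predict donor-site thickness can do both if it enters the outcome model, and here neither the described allocation nor the named model uses any.

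The trial is small, so sizeable chance differences in one factor or another are likely. The Sample size section plans for a between-group difference of 0.5 mm, and a contrast of arm means is exactly the quantity that carries such an imbalance. At stake are the precision of that contrast and its credibility if the arms turn out to differ in, say, age or graft depth.

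**Working it through.** **Inputs.** From Sample size: difference 0.5 mm, SD 0.5 mm, significance level 0.05 (taken as two-sided, since sidedness is not stated), power 0.9, 22 per group. Assumed: the correlation r between covariate and outcome, which the documents do not give, over the range 0.3 to 0.7.

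**1. The plan's own figure.** Normal approximation: n = 2 × (1.960 + 1.282)² × (0.5/0.5)² = 21.01, rounded up to 22. The t-test calculation needs 22.02 per group and gives power 0.900 at 22. The figure reproduces as an unadjusted two-group comparison.

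**2. How often chance imbalance arises.** The standard error of a standardised baseline difference is √(2/22) = 0.302 SD. P(|difference| > 0.5 SD) = 2 × [1 − Φ(0.5/0.302)] = 0.097, about 10% for one continuous factor.

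**3. What it does to an unadjusted arm difference.** Shift = r × imbalance × SD, with imbalance 0.5 SD and SD 0.5 mm. The last column is the type I error conditional on that imbalance, against a nominal 5%.

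| r (assumed) | Shift | Share of 0.5 mm | Conditional type I error |
|---|---|---|---|
| 0.3 | 0.075 mm | 15% | 6.8% |
| 0.5 | 0.125 mm | 25% | 9.6% |
| 0.7 | 0.175 mm | 35% | 13.2% |

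For smaller imbalances the conditional error falls slightly below 5% (4.8% at 0.3 SD and r = 0.5). Over all randomisations the unadjusted test keeps its 5%.

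**4. What it does to the interaction.** Suppose a covariate x adds b·x to thickness at every visit. The arm difference at each visit then contains the same term, b × (mean of x in one arm − mean of x in the other). The group × time interaction compares arm differences between visits, so with complete data this term cancels. Step 3 therefore applies to the group effect and to arm contrasts at a given visit. It touches the interaction only if the covariate alters the time course.

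**5. What adjustment gains, and its price.** For an arm comparison at one visit, the residual SD is 0.5 × √(1 − r²). With k covariates, the average variance inflation for N = 44 is (44 − 3)/(44 − 3 − k): 41/40 = 1.025 for one, 41/38 = 1.079 for three. Power from the non-central t with 42 − k degrees of freedom:

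| r, or joint R for three covariates (assumed) | Price ignored | One covariate | Three covariates |
|---|---|---|---|
| 0 | 0.900 | 0.892 | 0.876 |
| 0.3 | 0.925 | 0.918 | 0.904 |
| 0.5 | 0.963 | 0.958 | 0.949 |
| 0.6 | 0.982 | 0.979 | 0.973 |

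On variance alone, the break-even correlation is √(1 − 40/41) = 0.16 for one covariate, √(1 − 38/41) = 0.27 for three and √(1 − 35/41) = 0.38 for six. A short list is safer than entering every factor named.

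**The case against.** The strongest reply is that this is a one-paragraph summary in a journal article. Covariate lists are often left to the analysis plan, which is not shown, and nothing in the text rules adjustment out. A reader might infer that the trial will never adjust; the documents do not say that. What stands is narrower: the article does name its model and a fallback, without covariates, and gives the prognostic factors a different and weaker job.

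A reader might also infer that significance tests at baseline will act as a screen, so that a non-significant result gives false reassurance. No such test or rule is written. The general 0.05 level is not tied to baseline, and descriptive reporting fits the present wording.

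A third tempting reading is that the planned analysis is biased or underpowered. It is neither: steps 1 and 3 show the planned 90% power and the unconditional 5% error intact. The shifts are chance deviations given a particular imbalance. Nor may they be carried over to the interaction test, for the reason in step 4. The patient's own normal-skin thickness could well be just such a constant offset.

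Two practical points also stand. Some listed factors have little room to vary: eligibility and the Standardization section confine the site to the thigh, and time since graft is nearly constant. And normal-skin thickness is already in the plan as a comparison site, with no stated time of measurement, so it is not automatically a safe covariate.

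**Conclusion.** The point holds as a missed improvement in a stated model; it is neither an error in the sample size nor a threat to validity. Factors the protocol itself regards as important are compared at baseline and then have no stated part in the outcome analysis, and the described randomisation does not balance them.

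There is about a 10% chance per continuous factor of an imbalance above 0.5 SD. An imbalance of 0.5 SD moves an unadjusted arm difference by roughly 0.08 to 0.18 mm out of 0.5 mm. Power for a single-visit arm comparison would rise from 90% to about 92–98% with one covariate of correlation 0.3 to 0.6. All of this except the 10% rests on assumed correlations; if the chosen covariates predicted nothing, three of them would lower power to about 88%.

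**What to change.** State in the analysis section that the arm comparison of donor-site thickness is adjusted for two or three named covariates already recorded. Reasonable candidates are donor-site depth as fixed at harvest, age, and the patient's normal-skin thickness. The last should be used only if it is measured before the garment is applied or at an untreated site, and the protocol should say which. For erythema, adjust for Fitzpatrick skin type; a normal-skin erythema reading should not be assumed, because the article describes none.

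Name the covariates before outcomes are compared between arms and keep them whatever the baseline comparison shows. Report baseline characteristics descriptively. State that the adjustment serves the between-arm contrasts, since a constant offset leaves the group × time interaction unchanged.

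The cost is analysis wording and two or three degrees of freedom, with about 2 points of power lost in the worst case where three covariates carry no information. If normal-skin thickness is used, the timing or site of that measurement must also be fixed.

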### Measurement tools

In this study, the commercially available, evidence-based measurement tools described below will be used. These outcome measures will be done every 2 weeks for a period of 2 months.

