### Sample size

Previous studies using the DermaScan C have shown an effect size of 2.35 (1.69–3.01) between skin-thickness measurements of donor sites and scar sites [22]. For a minimum clinical difference of 0.5 mm between groups of less than 0.05 and a power of 0.9, 22 subjects per group would be required [22, 40] (assuming a standard deviation of 0.5 mm for wound thickness).

On the basis of data obtained from January 2013 to May 2015 (where patients admitted to the RBWH [name] Adult Burns Centre are represented as males = 593 admissions and females = 237 admissions), the ratio is expected to be 3:1. This ratio should accurately reflect the distribution of burns within the general community.

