### Trial status

Eight participants have been recruited to date for a pilot study. A total of 44 participants (22 for each group) is required.

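### The two-way ANOVA named for fortnightly skin thickness has no within-patient term. Run literally, its error rates are wrong. Run as a repeated-measures ANOVA, it is valid with complete data, but the SPSS procedure drops patients with a missed visit.

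*Protocol article*

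**What the plan says.** The section Proposed data analysis names one between-group outcome analysis, for skin thickness: "a two-way analysis of variance for group × time interaction will be performed". It adds least-significant-difference post hoc tests, a 0.05 significance level and SPSS 22.0. If the data are not normal, an equivalent non-parametric analysis is to be used.

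The data for this test are repeated. The section Measurement tools states: "These outcome measures will be done every 2 weeks for a period of 2 months". The section Intervention applies the schedule to everyone: "Both groups will be reviewed every 2 weeks over the 2-month period". That makes four follow-up visits, at weeks 2, 4, 6 and 8, or five measurements if a baseline is counted.

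No patient term, within-subject factor or repeated-measures procedure is named. The sentence also brings in skin site (normal, donor, scar) as a third classification in a model called two-way. Site also appears to be measured within the patient.

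**The concern.** Thickness readings from one patient at successive fortnights are correlated. A two-way ANOVA with group and time as its only factors has a single residual and treats every reading as a separate unit. It then tests the arm effect against too small an error and the interaction against too large an error. The trial could declare an arm effect that is not there, or miss a real divergence over time, which is the effect the plan sets out to test.

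The plan can also be read as a repeated-measures ANOVA. The concern there is different: the usual SPSS route needs every visit from every patient, and patients must keep coming back fortnightly after discharge.

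**Working it through.** **Inputs from the protocol article.** The section Sample size gives "minimum clinical difference of 0.5 mm between groups of less than 0.05 and a power of 0.9, 22 subjects per group would be required", "assuming a standard deviation of 0.5 mm for wound thickness". The section Trial status says: "A total of 44 participants (22 for each group) is required".

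**Assumptions, because the article gives no figure.** Within-patient correlation ρ is 0.3, 0.5 or 0.7, with compound symmetry. There are four visits, normal outcomes and equal variances. Tests are two-sided.

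**Step 1: the plan's own figure.** n per group = 2(1.960 + 1.282)² × (0.5/0.5)² = 21.01, rounded up to 22. Power of the two-sample t-test at 22 per group is 0.8997. The 22 is reproduced as a single two-group comparison of means and does not depend on the present point.

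**Step 2: visits treated as independent, no true effect.**
- Arm test: the true variance of an arm mean over T visits is σ²[1 + (T − 1)ρ]/(nT), but the model uses σ²/(nT). The F statistic is therefore inflated by about 1 + 3ρ, that is 1.9, 2.5 and 3.1. The rejection rate is about P(|Z| > 1.96/√(1 + 3ρ)). The cut-offs 1.422, 1.240 and 1.113 give 15.5%, 21.5% and 26.6%.
- Interaction test: the numerator has expectation σ²(1 − ρ), but the residual estimates σ². The rejection rate is about P(χ²₃ > 7.815/(1 − ρ)). The cut-offs 11.16, 15.63 and 26.05 give 1.1%, 0.14% and under 0.01%.

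Simulation with 20,000 runs per setting agrees:

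| ρ | Arm test, nominal 5% | Group × time test, nominal 5% |
|---|---|---|
| 0.3 | 15.8% | 1.3% |
| 0.5 | 21.4% | 0.2% |
| 0.7 | 26.9% | 0.0% |

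Over a wider range (ρ up to 0.8, AR(1) as well as compound symmetry, four or five visits), the arm test runs from 11.6% to 34% and the interaction test from 0% to 2.8%.

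**Step 3: power of the interaction test.** Take a difference growing in equal steps from 0.125 to 0.5 mm, that is 0.25, 0.50, 0.75 and 1.00 SD. The squared deviations from their mean of 0.625 sum to 0.3125. With the correlation modelled, the noncentrality is (22/2) × 0.3125/(1 − ρ) = 4.91, 6.88 and 11.46. On F(3, 126) this gives power of 42%, 57% and 81%. Simulated values, which vary by about one percentage point between runs, are:

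| ρ | Visits as independent | Correlation modelled |
|---|---|---|
| 0.3 | 23% | 43% |
| 0.5 | 15% | 56% |
| 0.7 | 8% | 81% |

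The trajectory is an assumption. For growth from 0 to 0.5 mm the figures are 47%, 42% and 35% against 69%, 83% and 97%. The level differs but the pattern is the same.

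**Step 4: repeated-measures ANOVA, complete data, no true effect.** For ρ from 0.3 to 0.8, the arm test rejects 4.7% to 5.2% in every setting. The interaction test rejects 4.8% to 5.3% under compound symmetry. Under AR(1) it rejects 5.2% to 8.0% uncorrected. Over all settings it rejects 4.3% to 5.3% with the Greenhouse-Geisser correction and 4.7% to 5.7% with Huynh-Feldt.

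**Step 5: missed visits under the SPSS repeated-measures GLM.** If each visit is missed independently with probability m, the share of patients dropped is 1 − (1 − m)⁴.
- m = 0.05: 1 − 0.95⁴ = 18.5%, leaving 22 × 0.815 = 17.9 per arm.
- m = 0.10: 1 − 0.90⁴ = 34.4%, leaving 22 × 0.656 = 14.4 per arm.

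Both rates, and independence between visits, are assumptions.

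**The case against.** The strongest reply is that the article never says visits are independent. A two-way ANOVA for group × time is common shorthand for a mixed ANOVA with patient as an error stratum, and the repeated design is plain elsewhere in the article. This stands. A reader might infer that the error rates are wrong whichever way the test is run. Step 4 shows they are not: with complete data the repeated-measures version is sound, given a sphericity correction where needed.

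Second, the 16% to 27% belongs to the arm main effect, while the plan names the interaction. This also stands. On the literal reading the named test loses power and does not create false positives.

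Third, covariance structure, sphericity correction and missing-visit rules are often left to an analysis plan, which is not shown. Their absence is not held against the article, and listwise deletion is a property of one software route, not a rule the article states. But the article does commit to a named test, post hoc method, significance level and package, and that test is invalid if followed as written.

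Two further inferences should be resisted.
- A reader might take power under listwise deletion to be 83% or 74%. Those are t-test powers for one visit at 17.9 and 14.4 per arm. The repeated-measures arm test averages four visits. At ρ = 0.5 the variance factor is (1 + 3 × 0.5)/4 = 0.625, so a constant 0.5 mm difference is 1/√0.625 = 1.265 SD, and power is about 96% and 90%.
- A reader might also suppose that attendance will differ by arm because only one arm wears a garment. That is possible, but both arms have the same review schedule and nothing in the article shows it.

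**Conclusion.** The point holds in this form: the named analysis leaves out the within-patient structure of the data it will be applied to. How much this matters depends on how it is run.

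Taken literally, the arm test is badly anti-conservative, and the interaction test is far too conservative with a large loss of power. The direction is the same for every positive correlation examined. The exact sizes rest on the assumed correlation, four visits and, for power, the assumed trajectory.

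Taken as a repeated-measures ANOVA, the error rates are acceptable with complete data. The remaining weakness is that incomplete attenders are discarded, on a scale set by missed-visit rates the article does not give. The stated total of 44 is exactly twice 22, so no allowance for such losses is visible.

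Because one permitted reading is invalid and the other can waste data, the wording should be settled before analysis.

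**What to change.** Replace the two-way ANOVA with a linear mixed model for donor-site thickness:
- fixed effects for arm, visit and arm × visit;
- unstructured within-patient covariance, with compound symmetry as the stated fallback if that does not converge;
- all available visits from every randomised patient, with no listwise deletion;
- if normal and scar sites are included, site as a further within-patient factor.

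Report the week-8 arm difference with its 95% CI. That contrast matches the sample size calculation, which is for a between-group difference. The interaction test does not match it: for a constant 0.5 mm difference it rejects only about 5% of the time, even in the repeated-measures ANOVA.

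The MIXED procedure is part of SPSS, so no new software is needed. The cost is a change of analysis wording and slightly more analyst time. Visits, measurements and sample size stay as they are.

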**Table Taba:** 

*Inclusion criteria*	*Exclusion criteria*
Donor site located on one thigh only (measured to be 10 cm above the patella)	Burns to left, right or both thighs
Male or female	Donor site at anatomic location other than the thigh,
Older than 14 years of age (with adult consent) and able to provide informed consent	A psychiatric history documented in the medical chart which could cause a variable outcome (high risk of non-compliance)
	A pre-existing co-morbidity associated with delayed healing
	Arterial disease and/or vascular compromise as previously documented in the medical chart
	A dermatological condition in the region where the donor site needs to be taken
	Allergy to ultrasound gel
	Medications that may impact on wound healing
	Consent not given

If eligibility is established, patients will be approached by the principal investigator and a lay explanation of the study procedures and requirements will be provided. Participants will be included once informed consent has been obtained and documented. Child assent will be documented where appropriate.

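### The only efficacy analysis sentence is internally inconsistent (group × time model, skin-site comparison), and its interaction test is not the between-arm difference for which the trial was sized

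*Protocol article*

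**What the plan says.** Under Randomisation, the groups are the two treatment arms: "Participants will be randomly allocated into one of two groups: a control group that will have no compression to donor sites", the other arm receiving compression. Primary objectives frames every aim as IPG against no IPG.

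Under Sample size, the trial is sized for a 0.5 mm difference between groups with an SD of 0.5 mm, "and a power of 0.9, 22 subjects per group would be required". The same section cites an effect size of 2.35 (1.69–3.01) for thickness at donor sites versus scar sites.

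Under Proposed data analysis, the opening sentence uses the word for the arms: "Groups will be compared at baseline regarding the important prognostic indications". The efficacy sentence then says that, if parametric methods are usable, "a two-way analysis of variance for group × time interaction will be performed", and gives its purpose as to "compare skin thickness between normal, donor and scar sites with a planned least significant difference post hoc analysis". Significance is set at p < 0.05. This is the only efficacy model in the article. It names no IPG-versus-control contrast in donor-site thickness and no time point for one.

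Under Measurement tools, outcomes are taken every 2 weeks for 2 months.

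**The concern.** A two-way model has two factors. Those named are group and time, yet the comparison named is among three skin sites. The analyst must decide what group stands for, and each choice conflicts with another part of the text. A choice left open here could end up being made after the data have been seen.

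On the more natural reading, group as arm, there is a second mismatch. A group × time interaction asks whether the arm difference changes between visits. The trial is sized for the size of the arm difference. If the garment gives the full 0.5 mm benefit by the first analysed visit and holds it, the interaction has nothing to detect. A working treatment could then give a non-significant result on the one test the plan states, and the 90% power would describe a different test.

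**Working it through.** **1. The two readings of group**

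| Reading | Factors in the two-way model | What is lost |
|---|---|---|
| Group = arm (usage in Randomisation, Intervention, Sample size and the opening sentence of Proposed data analysis) | arm, time, arm × time | Site is not in the model, so it cannot compare normal, donor and scar sites |
| Group = site (suggested by the purpose stated in the same sentence) | site, time, site × time | Randomised arm is not in the model |

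Neither reading yields the comparison described under Sample size.

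**2. The plan's own sample size**

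Inputs from Sample size and Proposed data analysis: difference 0.5 mm, SD 0.5 mm, alpha 0.05, power 0.90. Two-sided testing is assumed, as sidedness is not stated.

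n per arm = 2 × (1.960 + 1.282)² × (0.5/0.5)² = 21.01, rounded up to 22.

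The t-test version gives 22.02, and its power at 22 per arm is 0.900. A one-sided test gives 18. The cited effect size of 2.35 would give only 4 to 5 per arm. So 22 is correct, and it comes from a two-sided comparison of two arm means.

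**3. Power of the stated interaction on the arm reading**

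Inputs: n = 22 per arm and SD = 0.5 mm from the article. Assumed: compound symmetry and within-patient correlation ρ of 0.3, 0.5 or 0.7, since the article gives no correlation. Fortnightly measurement is taken as four visits, at weeks 2, 4, 6 and 8.

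With arm differences d₁…d_T over T occasions, the noncentrality of the repeated-measures interaction test is

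λ = (n/2) × Σ(d_t − d̄)² / [SD² × (1 − ρ)],

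with T − 1 and (T − 1)(2n − 2) degrees of freedom. Here n/2 = 11 and SD² = 0.25.

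- **Constant 0.5 mm, four visits.** Σ(d_t − d̄)² = 0, so λ = 0 and power equals alpha.
- **0.125, 0.25, 0.375, 0.5 mm, four visits.** Mean 0.3125, sum of squares 0.078125. At ρ = 0.3, λ = 11 × 0.078125 / 0.175 = 4.91. At 0.5 and 0.7, λ = 6.88 and 11.46. Degrees of freedom 3 and 126.
- **Pre-treatment difference of 0, then 0.5 mm at four visits.** Mean 0.4, sum of squares 0.16 + 4 × 0.01 = 0.20. At ρ = 0.3, λ = 11 × 0.20 / 0.175 = 12.57. At 0.5 and 0.7, λ = 17.60 and 29.33. Degrees of freedom 4 and 168.

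| Pattern of benefit | ρ = 0.3 | ρ = 0.5 | ρ = 0.7 |
|---|---|---|---|
| Constant 0.5 mm, four visits | 5% | 5% | 5% |
| 0.125 to 0.5 mm, four visits | 42% | 57% | 81% |
| Pre-treatment 0, then constant 0.5 mm | 81% | 93% | 99.6% |

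In all three patterns the arms differ by 0.5 mm at week 8, so a two-sample comparison at that visit has 90% power throughout.

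**The case against.** The strongest reply is that the arms are in the model. The article uses group for the randomised arm throughout, so a group × time interaction tests whether thickness evolves differently under IPG and control, which is an IPG effect. This stands. A reader might infer from the site wording that the plan omits any arm comparison; the text does not support that.

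Other tempting arguments also fail:

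- **Least-significant-difference tests.** They might be taken to show that site is the tested factor, since they need three or more levels. Time has at least four levels, so they could equally apply to visits.
- **The 2.35 effect size.** It might be said to make the headline test significant whatever IPG does. On the arm reading site is not tested; on the site reading the stated test is site × time, which a constant site difference does not make significant.
- **Anatomy.** The eligibility table excludes "Burns to left, right or both thighs", so a scar site might be assumed to lie elsewhere on the body and be confounded with location. But the article also calls the healed donor wound a scar, and the analysis sentence does not say which is meant.
- **The 5% power figure.** It holds only if no pre-treatment measurement enters the model. The article does not settle this: Measurement tools says only every 2 weeks, while the Abstract calls the fortnightly visits follow-up.

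A two-way analysis of variance would also ordinarily produce a group main effect, with power of about 96% to 99.7% for a constant 0.5 mm over four visits under the same assumptions. However, the plan names the interaction, not the main effect. Finally, a fuller analysis plan may exist, and contrast and time point are often left to it. That would excuse missing detail. It does not reconcile a sentence whose model and stated purpose conflict.

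**Conclusion.** The point holds in this form: the efficacy sentence contradicts itself, and on its most natural reading the stated test is not the one behind the sample size. The contradiction follows from the text alone.

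The power range, from 5% to 99.6%, rests on the article's SD and sample size plus assumed compound symmetry, correlations of 0.3 to 0.7 and illustrative effect patterns. Its message is not that the interaction test is necessarily weak, since in some settings it exceeds 90%. It is that power depends on the correlation, the shape of the effect over time and the use of a pre-treatment measurement, none of which the article fixes. The 90% figure therefore cannot be attached to it.

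The sample size of 22 per arm is not in error. This should be corrected before the main analysis; Trial status reports eight participants recruited so far, for a pilot study, out of 44 required.

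**What to change.** Replace the efficacy sentence with wording such as: *The primary analysis estimates the difference in donor-site thickness between the IPG and control arms, with 95% CI, at one prespecified time point (for example week 8, the end of treatment), from a repeated-measures model with arm, visit and arm × visit.* State that comparisons among normal, donor and scar sites are descriptive, and say which tissue scar site refers to. State also whether a pre-treatment thickness measurement exists and how it enters the model.

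Week 8 is a suggestion: the article names no primary time point, so the investigators must choose one. The sample size stays at 22 per arm, and no patients or measurements are added. The cost is rewording and committing to one time point.

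### The planned ANOVA is dropped for an unnamed non-parametric analysis if the raw data are non-normal; the assumption concerns residuals, so a valid model can be displaced and the question changed.

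*Protocol article*

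**What the plan says.** In the protocol article, Proposed data analysis, the data are to be "tested for normality of distribution". What follows depends on the result. "If parametric statistics are able to be used", then "a two-way analysis of variance for group × time interaction will be performed to compare skin thickness between normal, donor and scar sites", with least significant difference comparisons afterwards. Otherwise: "If raw data are not normally distributed, an equivalent non-parametric analysis will be used". The section does not give the normality test, its level, or the set of values to be tested (each group and visit, each site, or everything together). It does not mention residuals or name the fallback.

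The Sample size section cites an effect size of 2.35 (1.69–3.01) "between skin-thickness measurements of donor sites and scar sites". It bases 22 per group on a 0.5 mm difference with an SD of 0.5 mm.

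**The concern.** An ANOVA assumes that what remains after fitting its terms is roughly normal. Raw values still contain the site, group and visit effects that the model is there to estimate. A distribution made of several shifted normal parts can fail a normality test although every part is normal. The trigger can then respond to the effects under study rather than to a fault in the model.

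The second difficulty is where the switch leads. The parametric branch is aimed at group × time. If the unnamed equivalent turned out to be a Mann-Whitney test at a visit or a Friedman test within each group, neither would test that interaction. The hypothesis tested would then depend on the data, and the choice of normality test, pooling and fallback could be made with the data in view.

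**Working it through.** **The plan's own figure.** n per group = 2(1.960 + 1.282)² × (0.5/0.5)² = 21.01, rounded up to 22. This agrees with the Sample size section (two-sided 5% assumed). Exact t-test power at 22 per group is 0.8997. The sample size is not in question.

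**Why raw data can mislead.** Work in units of the within-site SD. Suppose normal skin and donor site share a mean and scar lies 2.35 higher, with one third of the values from each site.
- Variance between sites = 2.35² × (1/3)(2/3) = 1.227.
- Total variance = 1 + 1.227 = 2.227, so site differences make up 1.227/2.227 = 55% of the raw variance.
- Third central moment = 2.35³ × (1/3)(2/3)(1/3) = 0.961.
- Skewness of the raw data = 0.961/2.227^1.5 = 0.29. Skewness of the residuals = 0.

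**How often a needless switch occurs.** From the documents: 44 participants, measurements every 2 weeks for 2 months (read as four visits), three sites, the separation of 2.35 and its limits. Assumed: Shapiro-Wilk at 5%, exactly normal errors, within-patient correlation 0.5. In the three-site rows 2.35 SD is placed between normal skin and scar. The article gives it between donor and scar, so only the setting with donor equal to normal matches the cited gap. Ranges across a row reflect the donor position, whether the patient effect is shared across sites, and simulation error.

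| Values given to the normality test | Switch although errors are normal |
|---|---|
| One group at one visit (22 values) | 5% |
| Both groups pooled, 0.5 mm apart, one visit | 5% |
| One site, one visit to four visits pooled | about 5–8% |
| Each group-visit cell, any rejection counts: 8 cells | 34% (1 − 0.95⁸ = 34%) |
| Same with 10 cells (baseline added) | 41% (1 − 0.95¹⁰ = 40%) |
| Two sites pooled, 1.69 / 2.35 / 3.01 SD apart | 5% / 20% / 67% |
| Three sites pooled, one visit | about 4–8% (donor midway) to about 50% (donor equal to normal) |
| Three sites, four visits pooled (528 values), donor midway | 26–40% |
| Same, donor 0.5 SD above normal | 84–88% |
| Same, donor equal to normal | 97–99% |

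**What the fallback would test.** These checks use 22 per group, SD 0.5 mm and four visits.
- Constant 0.5 mm group difference, hence no interaction: Mann-Whitney at the last visit is significant in 89% of trials; the interaction contrast (t-test on last minus first visit) in 5%.
- Same 0.25 mm change over time in both groups, again no interaction: separate Friedman tests disagree on significance in 48% of trials.
- Mann-Whitney on within-patient change does address differential change. With normal data its type I error is 0.048 and its power 0.89, against 0.90 for the t-test. With skewed (lognormal) data its power is 0.96 against 0.75.

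**Cost of the two-stage rule itself.** In a simple two-group case with normal data (t-test if both groups pass, Mann-Whitney otherwise), type I error is 0.052.

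**The case against.** Much can be said for the plan. The article never says that sites and visits will be pooled for the normality test. If one site is tested alone, needless switching is only about 5–8%, hardly more than the level of the test. The fallback could be a good one: ANOVA-type rank statistics for longitudinal designs, aligned ranks, permutation tests and rank tests on change scores can all address group × time, and with skewed data a rank test of change can beat the t-test. Naming the test and the fallback is also commonly left to a full protocol or an analysis plan, neither of which is shown.

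Most of this stands, and it rules out several stronger readings. A reader might infer that no non-parametric equivalent exists for an interaction; that is wrong. A reader might take the rates near 98% as the expected rate for this trial; they belong to one way of pooling that the article does not state. A reader might also infer an inflated false-positive rate, but 0.052 in the simple case shows no material inflation. Nor can the switch be said to cost covariate adjustment or a confidence interval, because this section promises neither.

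The defence does not reach the rule itself. Making the analysis depend on normality of raw data is stated in the article, not left open. An analysis plan would have to overturn that sentence, not merely complete it.

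**Conclusion.** The point holds in a limited form. The trigger examines the wrong quantity, and the analysis it leads to is unnamed and may or may not test group × time. With normal errors, the chance of discarding a valid model runs from about the nominal 5% to nearly certain, depending on an unstated choice of what is tested. Those rates rest on the assumed test, level, correlation and site means given above. They show how sensitive the rule is and do not predict what this trial will do. The matter deserves correction because it governs the only treatment comparison that the section describes. It does not invalidate the design.

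**What to change.** Delete the switching sentence and the condition placed on the parametric analysis. Name one repeated-measures model as the primary analysis whatever a normality test on raw data shows, for example a mixed model with group, visit and group × visit. If several sites stay in one model, include site as a term so that site differences do not enter the residuals. Judge the assumptions on residuals. Name one alternative in advance (the same model on log thickness, a permutation of arm labels, or a rank-based test of within-patient change) and report it as a sensitivity analysis beside the primary result, not in place of it.

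The cost is analysis wording only. The 22 per group, the visits and the measurements do not change. The Trial status section reports eight participants recruited for a pilot against the 44 required, so at that stage the wording could be settled before the main data are seen.
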